#### Flyers, social media, and radio

Flyers were placed in high traffic areas of the main VAPORHCS hospital and at two outpatient clinics and shared with local clinicians, study sponsors and other partners for broad dissemination. A social media post for LION was placed on the MTBI^2^ blog that also contributed participants to the overall TROOPS referral program. Other approved social media venues included Craigslist advertisements, GovDelivery (a marketing subscription email service), and other VA-approved accounts. IRB-approved visual banners and audio ads that aired on local AM radio stations were also utilized to recruit participants within the Portland-metro area. See Table 1 for the number of participants recruited via each approach.

**Table 1 pone.0305305.t001:** Interim demographic information for participants who have completed this protocol.

	MBLT (*n* = 69)		Sham (*n* = 35)	
	mTBI (*n* = 47)	No TBI (*n* = 22)	mTBI (*n* = 24)	No TBI (*n* = 11)
**Age,** *years*	53.2 ± 13.1	53.2 ± 14.8	50.9 ± 14.6	57.9 ± 15.9
**Education,** *years*	16.4 ± 1.9	15.8 ± 2.1	15.2 ± 1.9	16.2 ± 1.9

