**Modality**				
Remote (DocuSign consent)	39 (83%)	17 (77%)	20 (83%)	5 (45%)
In-Person (Physical copy consent)	8 (17%)	5 (23%)	4 (17%)	6 (55%)

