### Statistical analyses

The statistical analysis plan was designed to be carried out using GraphPad Prism v9 or R, with alpha defined *a priori* at 0.05, using a thorough descriptive analysis of participant baseline characteristics prior to evaluation of outcomes. Categorical variables will be described using frequencies and percentages. Histograms and boxplots will be used to assess the distribution of continuous variables. Continuous variables that follow an approximately normal distribution will be summarized using means and standard deviations; skewed continuous variables will be reported as medians and interquartile ranges. Potential covariates will also be summarized with descriptive statistics and graphs. As part of our descriptive analyses, we will compare participants who complete versus drop out of the study by baseline characteristics and study arm to ascertain potential biases that may impact this and future studies. Effect size estimates will be reported as Cohen’s d (small = 0.2; medium = 0.5; large = 0.8) or standardized regression coefficients (β) (small = 0.14; medium = 0.39; large = 0.59). We will also report the number needed to treat (NNT) approximated using methods described by Kraemer and Kupfer [71]. The Benjamini-Hochberg procedure will be used to control the false discovery rate for primary outcomes. Statistical outliers will be identified using regression diagnostics to estimate Cook’s Distance, and then a cutoff of 4/n (n = number of participants) will be used to identify outliers. Outliers will be examined for data entry errors, but otherwise retained in analyses. If data violate parametric assumptions via Shapiro-Wilk test, test statistics will be derived using robust standard errors. We will use the intent-to-treat principle and include all participants randomized to treatment irrespective of treatment compliance.

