LION was originally conceived as, and initiated in, an in-person format typical for device-based randomized controlled trials. However, in response to the COVID-19 pandemic, this protocol was revised to enable its execution in a fully remote capacity. The remotely executed randomized clinical trial format is innovative in and of itself, but especially so considering this protocol was implemented within the VA. Indeed, success with this current design was the result of many years of preparation in establishing standard operating procedures, integrating VA regulatory, clinical, the Office of Information Technology, information security/privacy, biomedical, mailroom, and other services within the local and national VA system, as well as refinement of the protocol to reduce burden and enhance the participant experience. Specific aspects of this study protocol that were novel and logistically critical to its success include: 1) The implementation of an electronic digital signature service (DocuSign) for obtaining informed consent. This enabled research coordinators to screen, consent, and schedule future visits all on essentially the first point of contact, capitalizing on participant motivation and minimizing the potential for errors or PHI/PII exposure. 2) Establishing the logistical workflow for shipping equipment to and from participants’ place of residence in a manner that minimized participant burden and enabled transfer of biospecimens. 3) Effective utilization of video conferencing technology. 4) Establishing multiple recruitment modalities to effectively reach participants nationwide. 5) Leveraging the digital distribution (via TWILIO^™^ and REDCap) of key outcome measures (e.g., all participant questionnaire data and sleep diary entries), with automatic data entry directly into REDCap.

The present rate of participant retention (83%) either exceeds or is on par with other randomized clinical trials of similar scale and complexity, e.g., Lam et al: 81% [28]; Youngstedt et al: 68% [45]. Additionally, these metrics should also be viewed in the context of this protocol being in a fully remote format, which could potentially introduce additional sources of error and/or opportunity for drop out. Accordingly, the present interim analysis refutes this possibility, demonstrating strong protocol feasibility for the remote implementation of morning bright light therapy in Veterans.

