Secondary outcomes in the proportion of participants with complete data were the entire self-reported questionnaire battery, neurocognitive assessment, DLMO, and biospecimen sample. For each of these metrics, all study groups at all time points report ≥75% data completeness defined as 1) no missing questions in the questionnaire battery, 2) all cognitive assessment tests complete, 3) seven DLMO salivettes for each time point, and 4) sweat and/or blood samples for each time point. The majority of outcomes were ≥83% complete, with many at 100%. Only one category, non-TBI sham participants post-intervention, reported a lower than expected rate of biospecimen sampling (60%). This is a small subset of participants (n = 10 in total), and thus, likely reflective of normal variability rather than potential bias in study coordinator/participant interaction. In summary, this interim analysis demonstrated that in the current sample of n = 104 participants, we have complete data in key outcome measures in >90% of participants, which also aligns with 80–85% of the sample reporting full device compliance. Thus, remotely implementing this randomized controlled trial has not introduced any significant increase in missingness or data incompleteness.

An additional benefit extending from the remote implementation of this trial was our ability to extend recruitment to anyone within the United States. This greatly increased our reach and anecdotally expanded enrollment to participants who would otherwise be unable or unwilling to participate in research. Similarly, nationwide recruitment also conferred a significantly greater degree of racial and ethnic diversity than would otherwise be feasible to accomplish with recruitment confined to the Portland, OR / Vancouver, WA metro area. Indeed, 34.9% of participants identified as female, 23.6% identified as belonging to a racial minority group, and 9.4% identified as Hispanic or Latino. According to the US Census Bureau (2021), 10% (~1.67 million) of Veterans identify as female, 25.8% (~4.17 million) identify as an individual from a racial minority group, and 8.6% (~1.4 million) identify as Hispanic or Latino. Thus, the present trial generally met or exceeded these US Census Bureau defined Veteran demographic statistics. Appreciating that the nationwide Veteran demographic will continue to increase in racial/ethnic diversity over time, we will continue to prioritize recruiting these traditionally under-represented populations.

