In conclusion, the present study protocol described the remote implementation of a placebo-controlled participant-masked randomized controlled trial within the VA. Herein we outlined the process by which the remote implementation was achieved and highlight overall study feasibility and acceptability through an interim analysis describing a high degree of participant compliance, device adherence and meeting criteria for providing complete data across all time points. Indeed, remotely implementing a randomized controlled trial imposed significant challenges but this did not compromise data fidelity, integrity, or completeness, as evidenced by the feasibility data reported herein. Data collection is on track to be completed by September 2024 with full efficacy analyses and future directions/applications forthcoming.

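### The article concludes that remote delivery did not raise drop-out or missing data, but it compares no retention, adherence or completeness figure between remote and in-person participants

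*Protocol article*

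**What the plan says.** Three statements in the Discussion concern the effect of remote delivery.

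- On drop-out and error, after noting that a remote format could add both: "Accordingly, the present interim analysis refutes this possibility, demonstrating strong protocol feasibility for the remote implementation". The support is overall retention of 83%, set beside 81% and 68% in two other trials.
- On missing data: "remotely implementing this randomized controlled trial has not introduced any significant increase in missingness or data incompleteness". The support is a completeness figure above 90% in key outcomes for all 104 participants together.
- In the closing paragraph: "this did not compromise data fidelity, integrity, or completeness, as evidenced by the feasibility data reported herein".

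Overview and ethics makes the feasibility and acceptability of a fully remote trial the secondary aim. Results calls evaluating them a central goal of the article.

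Table 1 classifies modality by type of consent, with a row labelled "Remote (DocuSign consent" and a row for in-person, physical-copy consent. Its population is given as "Interim demographic information for participants who have completed this protocol".

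**The concern.** Each statement says that completeness or retention under remote delivery is no worse than it would otherwise have been. That needs a comparison with in-person delivery and some bound on the difference, and the article reports neither. Table 3 splits adherence and completeness by arm and TBI history, never by modality. The p-values in Results are for active versus sham. The external benchmarks come from a light-therapy trial in depression and one in Veterans with PTSD. They do not show what this trial's retention would have been in person.

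The trial began in person, so an internal comparator exists in some form. It is small, and failing to find a difference with it would say little.

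At stake is the article's main reported result. Planners of later remote VA trials could cite these sentences as evidence that remote delivery costs nothing in retention or completeness, when that was not examined.

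**Working it through.** **Inputs**

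- Remote, Table 1: 39 + 17 + 20 + 5 = 81.
- In-person (physical-copy consent), Table 1: 8 + 5 + 4 + 6 = 23. Total 104.
- Retention, Results: 140 consented, 24 withdrawn or terminated, 12 ongoing.
- Post-intervention ISI present, Table 3: 43 + 17 + 21 + 10 = 91 of 104, so 13 missing.
- Significance level, Statistical analyses: "with alpha defined *a priori* at 0.05". I take the test as two-sided.
- In-person missing rate: not in the article. Assumed, 5% to 20%.

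**1. Retention.** (140 − 24)/140 = 116/140 = 82.9%, which reproduces the stated 83%. The Wilson interval is

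[p + z²/2n ± z√(p(1−p)/n + z²/4n²)] / (1 + z²/n).

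With p = 0.8286, n = 140, z = 1.96: (0.8423 ± 0.0639)/1.0274 = 0.758 to 0.882, or 76% to 88%. It contains the 81% benchmark and values 5 points below it. The 116 include the 12 ongoing participants, who could still leave. Setting them aside gives 104/128 = 81%, Wilson 74% to 87%.

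**2. Chance of missing a real rise in missing data.** For in-person rate p and true rise d, sum over all outcomes:

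P(miss) = Σᵢ Σⱼ Bin(i; 81, p + d) · Bin(j; 23, p) · 1{test p-value > 0.05}.

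| Assumed in-person missing rate | Fisher, 10-point rise | Fisher, 15-point rise | Uncorrected chi-square, 10 points | Uncorrected chi-square, 15 points |
|---|---|---|---|---|
| 5% | 89% | 69% | 82% | 62% |
| 10% | 89% | 74% | 85% | 70% |
| 15% | 89% | 76% | 86% | 72% |
| 20% | 89% | 77% | 86% | 73% |

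Power with Fisher's test is therefore about 11% for a 10-point rise and 23% to 31% for a 15-point rise.

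**3. A check from printed counts.** Suppose all 13 missing post-intervention ISI scores were remote: 13/81 = 16% versus 0/23. Two-sided Fisher gives p = 0.067. On that test, the most extreme split of these data against remote delivery would still count as no significant increase. The uncorrected chi-square gives p = 0.040, so this result is specific to Fisher's test.

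**The case against.** **The statements are descriptive commentary.** Results says that formal analyses across groups and outcomes have not been done, and it defines feasibility and acceptability through retention, adherence and completeness. Read as external benchmarking, 83% being on a par with 81% is fair, and the interval agrees. This stands for the retention sentence itself. It does not cover the further step of saying that the possibility of extra drop-out is refuted, or that remote delivery brought no significant increase in missing data. Reading significant in its everyday sense does not help, since no difference of any size was estimated.

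**The power figures describe a test that nobody ran.** They rest on assumed in-person rates and on the choice of test. True, and they should be quoted with those assumptions. The chi-square misses somewhat less often. One-sided Fisher misses 81% to 84% of 10-point rises and 58% to 69% of 15-point rises. An unpooled normal approximation gives 62% and 35% at a 5% in-person rate, but with 23 × 0.05 ≈ 1 expected event it is unreliable.

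**The 81 and 23 do not describe drop-out.** Correct. A reader might carry the 69% to 89% over to drop-out. The article does not support that: Table 1 covers completers, and the modality split of the 140 consented is not given.

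**The 23 may not all be in-person.** Also correct. Screening and informed consent allows paper forms by mail with a phone call, and dates DocuSign in the VA from March 2021, whereas Secondary: Biomarkers puts the move to a fully remote protocol at March 2020. Some physical-copy consents may belong to remote participants. A smaller true in-person group would generally make a comparison weaker still.

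**Conclusion.** The point holds in this form. Three conclusions about the effect of remote delivery rest on pooled rates, active-versus-sham tests and two external trials, with no remote versus in-person comparison. That part needs no assumption.

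The size applies to missing data among the 104 completers only. A two-sided Fisher test at 0.05 would miss a 10-point rise about 89% of the time and a 15-point rise about 69% to 77%, given in-person missing rates of 5% to 20% and the consent-based split of 81 and 23. For drop-out, all that can be said is that retention is 83% (76% to 88%), with the 12 ongoing participants counted as retained.

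A reader might infer two stronger things. One is that remote delivery did increase missing data or drop-out; nothing in the article shows this. The other is that the data could never reveal a 15-point rise; power of 23% to 31% is low but not nil.

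Randomisation, the primary outcome, the sample size and the efficacy analysis are unaffected. The change is still worth making, because remote feasibility is a stated aim and the article's main reported result.

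**What to change.** Replace the three comparative statements with the observed rates and 95% confidence intervals: for example, retention 116/140, 83% (76% to 88%), with 12 participants still ongoing, and post-intervention ISI 91/104, 87.5% (Wilson 80% to 93%). Add one sentence saying that no remote versus in-person comparison was made or powered.

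If a comparison is kept, report the remote minus in-person difference in retention (from the 140 consented) and in post-intervention ISI completeness, each with its 95% confidence interval, from data already held. Define modality by how the study was actually delivered, not by consent type, and state that it is confounded with calendar time. Make no claim of no increase from a non-significant result. With these numbers the table would be descriptive only.

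The first change costs a few sentences. The optional table costs a reclassification of participants by delivery and two rows. The price is a weaker conclusion about remote delivery.
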